### Plans to promote participant retention and complete follow-up {18b}

Patients are given access to contact the meditation trainer and the investigators throughout the trial period to clarify doubts. Primary outcome data will be collected in patients who discontinue or deviate from the intervention protocol if consent is granted. Participants will be contacted by the investigators periodically and encouraged daily practice of meditation and documentation in the diary.

### Data management {19}

Data will be entered by a dedicated person who is blinded to the patient allocation. Double data entry will be performed and will be stored under password protection in a dedicated computer.

### Confidentiality{27}

All interviews will take place in a confidential room. Personal information is only gathered to ensure the correct identification of patients when issuing the investigation reports. It will not be shared with a third party without their consent, and all data gathered will be securely kept under the direct supervision of the investigators. All data gathered will be stored securely for 5 years and then destroyed. Only the principal investigator and supervisors will have the authority to access the data.

### Plans for collection, laboratory evaluation and storage of biological specimens for genetic or molecular analysis in this trial/future use {33}

All the blood samples taken will only be used for the intended test, and no genetic studies will be performed. Blood samples will not be sent abroad or given to a third party. All samples will be stored for a period of one month for the completion of the tests and securely destroyed. All the reports of the blood tests will be given to the patient with a copy kept with the investigators.

## Statistical methods

### Statistical methods for primary and secondary outcomes {20a}

Statistical analysis will be performed using SPSS v-23. Intention to treat analysis will be carried out. Data will be analysed using descriptive statistics (frequency distribution, mean) to demonstrate the distribution of data for each parameter. Comparative statistics will be used to compare the findings between the sample groups, within the sample and control. Correlation analysis will be conducted to assess the correlation between related parameters. Each of the outcomes will be analysed using multiple regression analysis to ascertain the differences between trial arms. A linear regression model for continuous variables and logistic regression for binary variables will be used.

### Data monitoring committee{21a}

An independent data safety monitoring committee was appointed comprising senior researchers who have no competing interests. Any adverse events occurring will be reported to the committee by investigators and will be independently assessed.

### Interim analyses {21b}

If serious adverse events related to the intervention are reported in the meditation arm, the data safety monitoring committee and the investigators will discuss and decide to terminate the trial. Thereafter, an interim analysis will be conducted from the available data. The ethics review committee and the Sri Lanka Clinical trial registry will have access to interim results.

### Methods for additional analyses (e.g., subgroup analyses) {20b}

Subgroup analysis of the primary and secondary outcomes will be performed according to the age, gender, duration of diabetes and baseline HbA1c.

### Methods in analysis to handle protocol nonadherence and any statistical methods to handle missing data {20c}

We are planning to conduct an intention-to-treat analysis. Therefore, primary outcome data of the participants randomized to the intervention but who did not adhere to the intervention will be imputed using multiple imputation methods [40] available in SPSS.

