### Additional consent provisions for the collection and use of participant data and biological specimens {26b}

On the consent form, participants will be asked if they agree to give biological specimens (blood) for the investigations that are explicitly mentioned. Should they choose to withdraw from the trial, data will be used for analysis only if they give permission. Participants will also be asked for permission for the research team to share relevant data, excluding any personal data when publishing the results.

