### Criteria for discontinuing or modifying allocated interventions {11b}

The study will be terminated if there are more psychological/behavioural adverse events reported in the meditation group than in the control group or if there is more than 60% drop-out rate from the meditation program. A strong request from participants will be another reason for termination.

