### Strategies to improve adherence to interventions {11c}

Participants will be given a diary to record the meditation practices done at home, which will be checked at each session, and instructions will be given. This will include a record of time spent meditating, problems that occurred, doubts, reasons for distraction, etc. Participants are expected to record their meditation practice daily on most days of the week between weekly sessions. The diary will be used as the tool to check compliance with the intervention.

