### Sample size {14}

Patients with type 2 DM will be randomized to meditation and waitlisted arms. The number of patients required was 86 in each arm, which was calculated on the basis of determining a 0.5% reduction in HbA1c in the meditation arm in comparison to the waitlisted arm. The basis of 0.5% reduction is derived from looking at several randomized controlled trials (RCT) which have shown a significant reduction of HbA1c in the meditation arm compared to control arm. The reduction of HbA1c were; 0.5% in Gainey et al. 2016 [4], 0.7% in Gregg et al. 2007 [25], 0.74% in Pearson et al. 2018 [26], 0.83% in Miller et al 2012 [27], 1.0% in Armani Kian et al. 2018 [28], 1.1% in Chen et al. 2020 [29]. According to a meta-analysis, most of the oral hypoglycaemic drugs lowered HbA1c by 0.5% [30] as well. Therefore, the effect size was taken as a 0.5% difference in the reduction of HbA1c indicating that the lowest significant reduction of HbA1c is 0.5%. A power of 70% and a 95% confidence interval with a drop-out rate of 20% were considered.

The following formula was used for sample size calculation:$$N=\left[\left(1/{q}_1+1/{q}_0\right)\ast {\left({Z}_{\alpha }+{Z}_{\beta}\right)}^2\right]/\left[{\left(E/S\right)}^2\right]$$

where

*N* = Sample size

*q*1 = Proportion of subjects in the meditation group

*q*2 = Proportion of subjects that are in the waitlisted group

*Z*_*α*_ = Critical value of the normal distribution at *α* (*α* is 0.05 and the critical value is 1.96)

*Z*_*β*_ = Critical value of the normal distribution at *β* (*β* is 0.3)

*E* = Effect size (0.5% difference in HbA1c between the two groups)

*S* = Standard deviation of HbA1c in the population (0.8%).

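### As written, non-adherence in the meditation arm, not a missing HbA1c, triggers imputation of the primary outcome, which conflicts with the promised intention-to-treat analysis and can overstate the benefit

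*Protocol article*

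**What the plan says.** Four places in the protocol article bear on this.

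- **Handling of nonadherence and missing data {20c}.** The section opens with "We are planning to conduct an intention-to-treat analysis" and gives the next step as its consequence: "primary outcome data of the participants randomized to the intervention but who did not adhere to the intervention will be imputed using multiple imputation".
- **Statistical methods for primary and secondary outcomes {20a}.** The same label appears: "Intention to treat analysis will be carried out".
- **Participant retention and complete follow-up {18b}.** "Primary outcome data will be collected in patients who discontinue or deviate from the intervention protocol if consent is granted".
- **Additional consent provisions {26b}.** For participants who withdraw from the trial, "data will be used for analysis only if they give permission".

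Adherence itself is read from the home-practice diary, section {11c}: "The diary will be used as the tool to check compliance with the intervention".

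**The concern.** An ITT analysis compares the arms as randomised, using each patient's outcome whatever treatment was actually taken. The sentence in {20c} does something else. It picks out patients by what they did after randomisation, in the meditation arm only, and substitutes modelled values for their primary outcome. It does not restrict this to patients whose HbA1c is missing, and {18b} implies that many of these values will be on file.

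An analyst who follows the sentence would discard observed randomised outcomes and report the result as ITT. The imputed values would be drawn from a model fitted without any non-adherent meditation patient. If those patients benefit less, or have worse glycaemic control for other reasons, the primary estimate leans towards meditation.

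**Working it through.** **1. The passages side by side.** {18b} collects HbA1c from patients who discontinue or deviate, subject to consent. {20c} imputes the HbA1c of patients who did not adhere. These groups largely coincide. An analysis that uses the collected values is ITT; one that imputes them because of non-adherence is not. The plan gives no figure for the rule, so there is none to reproduce.

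**2. Inputs.** From the sample size section {14}: 86 per arm (taken as stated), SD 0.8%, two-sided 5% (critical value 1.96), and "Effect size (0.5% difference in HbA1c between the two groups". The non-adherence rate is not given. I assume 20%, 40% and 60%: 20% equals the planned drop-out rate in {14}, and 60% is the drop-out limit in {11b}, which stops the study "if there is more than 60% drop-out rate from the meditation program". Also assumed: the baseline correlation (0.5), no benefit in non-adherers, and the size of any prognostic gap.

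**3. Expected estimates.** Let p be the non-adherent share, d the HbA1c reduction in adherers (none in others), and g the amount by which non-adherers' HbA1c would be higher anyway, in either arm. Adherence is taken as unrelated to baseline HbA1c.

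- ITT on observed values: (1 − p)·d
- The rule, arm in the imputation model: d + p·g
- The rule, arm left out: imputed values centre on the mean of all retained patients, giving 2(1 − p)(d + p·g)/(2 − p)

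With d = 0.5 and g = 0, arm left out, at p = 0.2: 2 × 0.8 × 0.5 / 1.8 = 0.444.

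| p | ITT | Rule, arm in model | Rule, arm left out |
|---|---|---|---|
| 20% | 0.40 | 0.50 | 0.444 |
| 40% | 0.30 | 0.50 | 0.375 |
| 60% | 0.20 | 0.50 | 0.286 |

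A simulation (regression adjusted for baseline, 20 imputations, Rubin's rules; 1,500 runs per cell with arm in the model, 800 without) agrees: ITT 0.40 / 0.30 / 0.21; rule with arm 0.50 / 0.50 / 0.51; rule without arm 0.45 / 0.38 / 0.29.

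**4. Benefit and prognosis together.** With d = 0.5, g = 0.3 and arm in the model, d + p·g is 0.56 / 0.62 / 0.68, and the simulation gives the same to within rounding. That exceeds even the effect in adherers.

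**5. Type I error when meditation has no effect in anyone (simulated).**

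| Prognostic gap g | Imputation model | 20% | 40% | 60% |
|---|---|---|---|---|
| 0 | arm included | 4.6% | 5.3% | 4.5% |
| 0.3 | arm included | 8.7% | 16.7% | 23.9% |
| 0.3 | arm left out | 5.8% | 4.0% | 1.9% |
| 0.5 | arm included | 13.8% | 32.5% | 52.4% |
| 0.5 | arm left out | 10.1% | 16.6% | 12.0% |

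ITT on observed values rejected in 3.5 to 5.4% of runs in the 1,500-run null cells, and in 3.9 to 7.4% in the noisier 800-run cells. At a true 5%, simulation error is about 1.96 × √(0.05 × 0.95/1500) = 1.1 points, and 1.5 points with 800 runs.

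**The case against.** The strongest defence is that the authors meant something ordinary. The heading of {20c} joins nonadherence with missing data, multiple imputation is a tool for missing values, and {18b} and {26b} make collection and use of data depend on consent. Read together, the plan may be to collect HbA1c where consent allows and impute it for patients lost along with their non-adherence. No sentence says that an observed value will be deleted. That reading is possible and I cannot exclude it, but {20c} does not say it: the word missing appears only in the heading, and the condition in the text is failure to adhere. The wording needs correcting on either reading.

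The defence is right on the following points, where a reader might infer more than the documents support.

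- **That the rule always inflates false positives.** It does so only if adherence predicts HbA1c beyond what the imputation model contains. Without that, the error stays near 5%. With arm left out of the model and a 0.3% gap, there is no material inflation.
- **That the rule estimates the effect in adherers.** This is exact only if adherence is not prognostic and arm is in the imputation model. Otherwise the estimate can overshoot that effect (step 4) or fall between it and the ITT effect (step 3).
- **That one figure gives the size of the bias.** The article does not state the imputation model. A complete lack of benefit in non-adherers is an extreme assumption, and a 0.5% gap is as large as the whole target effect. The 40% and 60% rates are illustrations.
- **That the diary lets someone choose whose values are replaced.** The article gives no adherence threshold, but that is detail the full protocol or analysis plan may hold, and section {17a} blinds the data analysts. It is not part of this finding.

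**Conclusion.** The point holds as a fault in a stated rule, not as an omission. The text of {20c} ties imputation of the primary outcome to non-adherence in one arm. That contradicts the ITT analysis promised there and in {20a}, and it cannot be squared with using the HbA1c collected under {18b}. Followed literally, it does not estimate the ITT effect.

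The direction of the bias is conditional: it favours meditation if non-adherers benefit less or have worse HbA1c, which is plausible but not stated in the documents. With a 0.5% benefit confined to adherers, the rule reports about 0.45 to 0.50 against 0.40 at 20% non-adherence, 0.38 to 0.50 against 0.30 at 40%, and 0.29 to 0.51 against about 0.20 at 60%. With a prognostic gap of 0.3 to 0.5%, type I error is about 6 to 14% at 20% non-adherence. It can be higher with more non-adherence, depending on the imputation model.

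**What to change.** Replace the sentence in {20c} with:

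> All randomised patients are analysed in their allocated arm using their observed 3-month HbA1c whatever their adherence. Multiple imputation is used only where the 3-month HbA1c is missing (including where consent for collection or use is not given), in both arms, with arm and baseline HbA1c in the imputation model.

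If an effect-if-adherent estimate is wanted, present it as a labelled supplementary analysis with its assumptions stated.

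The cost is one sentence. No new data collection is needed, because {18b} already provides for HbA1c from patients who discontinue or deviate, subject to consent. The downside is that the estimated effect may be smaller than under the current wording.

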### Plans to give access to the full protocol, participant-level data and statistical code {31c}

The datasets analysed during the current study and statistical codes are available from the corresponding author on reasonable request, as is the full protocol.

## Oversight and monitoring

### Composition of the coordinating centre and trial steering committee {5d}

The coordinating centre will be the Department of Physiology, Faculty of Medicine, University of Colombo, led by the Head of the department. The trial steering committee will comprise of investigators and medically qualified research assistants. The role and responsibility of the coordinating centre and trial steering committee will be, to coordinate patient recruitment, provide support with coordinating appointments for investigations, provide day-to-day liaison service and solve technical issues. The steering committee will closely monitor technical officers regarding maintenance of equipment and supply of consumables. The research promotion and facilitation centre (RPFC) of the Faculty of Medicine, University of Colombo, will provide oversight. The trial steering committee will meet once a month over the course of the trial to discuss the progress.

The progress report will be submitted periodically to the ethics review committee and research and higher degrees committees.

### Adverse event reporting and harms {22}

Patients will also be monitored throughout the study for any adverse events related or unrelated to meditation (e.g., adverse effects of anti-diabetic drugs). Their health and well-being will be assessed through clinical assessment and monitoring of investigations. Serious adverse events will be monitored by the data safety monitoring board and reported to the ethics committee and the treating physician. The necessary actions will be taken, including further investigations and management steps. Patients who suffer any serious adverse events will be monitored and followed up for an extended period of 2 years, regardless of whether they continue to be part of the study.

### Frequency and plans for auditing trial conduct {23}

The Project Management Group, comprising both the members from the coordinating centre and trial steering committee, will meet monthly to review the trial conduct. The trial Steering committee and the independent data safety monitoring board will meet monthly and if there are any issues reported to the Ethics Review Committee of the Faculty of Medicine, University of Colombo, throughout the trial period. Any protocol amendments will be duly notified to the Ethics Review Committee, and approval will be taken prior to implementation.

### Plans for communicating important protocol amendments to relevant parties(e.g., trial participants, ethical committees) {25}

Any amendments to the protocol will be communicated in writing to all participants, and consent will be taken from them prior to conduct. Approval for any protocol amendments will be taken from the Ethics review committee of the Faculty of Medicine Colombo and Sri Lanka Clinical trial registry.

### Dissemination plans{31a}

The individual results of the investigations will be shared with the relevant participant. The overall results of the trial will be published in peer review local and international journals and will be presented in scientific conferences. All investigators will be authors, and professional writers will not be involved.

## Discussion

We believe that this will be the first randomized controlled trial in Sri Lanka to assess the effectiveness of mindfulness meditation on the glycaemic control of type 2 diabetes. Although similar studies have been performed in other parts of the world, data from randomized control trials involving South Asians are lacking. As meditation intervention may have different outcomes in different populations, the results from our study will benefit the management of a growing population of patients with diabetes mellitus in our region. Furthermore, some of the possible mechanisms of how meditation brings about glycaemic control, such as its effect on autonomic function and gut transit time, will be studied for the first time in this trial. However, it is difficult to assess the generalizability and fidelity of the intervention across all patients as meditation is a highly individualised intervention which depends on multitude of factors. This is a shortcoming of this type of a clinical trial.

## Trial status

Trial status- Participant recruitment stage. The planned participant recruitment end date is the 30th of June 2023

## Data Availability

Only deidentified data will be shared after a written request made to the investigators, and only for meta-analysis following 3 months after publication. The public will be able to access the protocol.

## Abbreviations

DM: Diabetes mellitus
IDF: International Diabetes Federation
MBST: Mindfulness-Based Stress Reduction Therapy
MRI: Magnetic resonance imaging
FBS: Fasting blood sugar
S. Cr: Serum creatinine
ALT: Alanine transaminase
AST: Aspartate transaminase
ESR: Erythrocyte sedimentation rate
FBC: Full blood count
CART: Cardiac autonomic reflex testing
BMI: Body mass index
OCTT: Orocecal transit time
NHSL: National Hospital of Sri Lanka
NYHA: New York Heart Association
HRV: Heart rate variations
ECG: Electrocardiogram
MOCA: Montreal Cognitive Assessment
